| (e) | Details of procedure and methodology proposed to be used (300 words) including description of the potential risks and benefits, exclusion and Inclusion criteria outcome measures, statistical analysis:  ***Patient population:*** *Covid-19 positive symptomatic cases either non-severe or severe category*  ***Intervention:*** *Two therapeutic interventions for non-severe category and three for severe category as described below*  ***Comparator:*** *Parallel arm design, compared among other interventional arm in same category*  ***Outcomes:*** *Clinical and laboratory improvements in 72 hours of treatment*  **Patient population-**  Patients diagnosed with SARS-CoV-2 infection after positive reverse-transcriptase–polymerase chain reaction (RT-PCR) assay.  **Inclusion criteria:**   1. Age ≥18 years at time of participation in the study 2. Laboratory (RT-PCR) confirmed infection with SARS-CoV-2 3. Symptomatic (severe or non-severe) Covid-19 disease 4. Willingness of study participant to accept randomization to any assigned treatment arm   **Exclusion criteria:**   1. Use of medications that are contraindicated with Lopinavir/Ritonavir, Hydroxychloroquine/Chloroquine, or Ribavirin and that cannot be replaced or stopped 2. Patient already on antiretroviral therapy with Lopinavir-Ritonavir based regimen or on Hydroxychloroquine/Chloroquine or on Ribavirin 3. Any known contraindication to test drugs such as retinopathy and QT prolongation 4. Known allergic reaction or inability to delivery oraly to Lopinavir-ritonavir, Hydroxychloroquine/ Chloroquine, Ribavarin 5. Pregnant or breastfeeding females 6. Receipt of any experimental treatment for 2019-nCoV (off-label, compassionate use, or trial related) within 30 days prior to participation in the present study or want to participate after enrolment   **Potential benefits:**   1. All those who participate in the trial will benefit from possible effective treatment for COVID-19 infection 2. The study will highlight the therapeutic options in management of the symptomatic patients of COVID-19 infection   **Potential risks:**  The present study will be conducted on symptomatic patients of COVID-19 attending AIIMS Rishikesh. The patients will be categorised based on severity and treatment will be allocated accordingly.  Adverse drug reactions, though not frequent may be associated with the treatment. Proper supportive management will be given to the patients at the institute.  **Methodology**:  **Flow Diagram**  Patients of COVID-19 infection - After confirmation by RT-PCR at AIIMS, Rishikesh  Screening for inclusion in trial Enrolment Excluded  ♦  Not meeting inclusion criteria  ♦  Declined to participate  ♦  Other reasons  Categorisation based on severity of patient  **SEVERE group**  **NON-SEVERE group**  Randomisation to treatment arm:  **A. Standard Treatment (ST-S)**  **B. Hydroxychloroquine + Ribavirin + ST-S**  **C. Lopinavir+ Ritonavir + Ribavirin + ST-S**  Randomisation to treatment arm:   1. **Standard Treatment (ST-NS)** 2. **Hydroxychloroquine + Ribavirin + ST-NS**  RandomisationAllocation Monitor progress of patient in 72 hours Follow-Up Patient improve- continue same treatment  Clinical evaluation- @72 hours  Improve - Continue same treatment  Progress – achieved end point and Shift to institute protocol for further treatment  Patient do not improve/ Signs of severe disease  Shift to **SEVERE group** treatment arms after randomization with new consent Analysis Analysis  **Total duration of observation**:  28 days from the time of enrolment into the study OR till patient is discharged or death whichever is longer  **Design:** Open label, Parallel arm design, stratified randomised controlled trial:  Patients will be screened for the study after diagnosis of COVID-19 infection by Microbiology team. Patients will be categorised as non-severe or severe based on predefined criteria. The patient will be enrolled in the study after a written informed consent. Since it is an exploratory trial as COVID-19 being a new disease, all patients who came under the purview of the inclusion criteria within the study period and who have consented for the study will be included. Clinical evaluations will be done by a separate investigator. Blinding will not be performed but dynamic randomization will be done. Patients will be followed up for a period of 28 days from the day of enrolment.  At the time of enrolment, demographic information will be collected from participants, and relevant data on their medical histories, comorbidities, and risk factors for severe COVID-19. It will be documented along with investigations including CBC, ECG, LFT, RFT, G6PD status.  The patients will be categorised as severe based on the following criteria:   - Confirmed pneumonia on chest imaging, SPo2 <93%, Pao_2_:Fio_2_ <300 mg Hg - Respiratory failure (need of mechanical ventilation) - Septic shock - Multiple (>2) organ dysfunction syndrome (MODS) - Liver disease (Child Pugh score ≥ C, AST>5 times upper limit) - Patients with known renal impairment (estimated glomerular filtration rate ≤30 mL/min/1.73 m2) or receiving continuous renal replacement therapy, haemodialysis, peritoneal dialysis - Other single organ failure (e.g. heart, pancreas, etc) if specific definition meets   Non-severe category includes mild and moderate disease severity category other than severe ones.  **Treatment Schedule**  **Non-severe Treatment arms (NS-group):**   \| **Treatment Arm** \| **Drug** \| \| --- \| --- \| \| A \| Standard Treatment (ST_NS_) \| \| B \| Hydroxychloroquine 400 mg twice on first day followed by 400 mg per oral daily for 10 days + Ribavirin (2.4 g orally as a loading dose followed by 1.2 g orally every 12 hours) for 10 days + Standard Treatment (ST_NS_) ^6^ \|   **Standard Treatment for non-severe cases (ST_NS_):**   1. Strict Isolation 2. Standard Precautions (Hand hygiene, Cough Etiquette, Wear surgical mask) 3. Hydration 4. Proper Nutrition 5. Supportive Pharmacotherapy (Antipyretic, Antiallergic, Cough Suppressant) 6. Treatment of Comorbid Diseases 7. Oseltamivir (75 mg BD) for patient who are tested positive for H1N1   If the patient improves clinically the same treatment will be continued. If the patient do-not improve or shows sign of severity (mentioned above) the patient will be shifted to the severity arm (S-group) of the clinical trial and again randomization will be done and enrolled after new consent only for severe group. However, if intervention falls on HCQ arm, then it will be taken as end point reached and shifted to institute treatment protocol for further management.  **Severe group Treatment arms (S-group):**   \| **Treatment Arm** \| **Drug** \| \| --- \| --- \| \| A \| Standard Treatment (ST_s_) \| \| B \| Hydroxychloroquine 400mg BD on day1 followed by 400 mg once daily + Ribavirin (2.4 g orally as a loading dose followed by 1.2 g orally every 12 hours) for 10 days + Standard Treatment (ST_s_) \| \| C \| Lopinavir(400mg) + Ritonavir (100mg) two tablets twice daily+ Ribavirin (2.4 g orally as a loading dose followed by 1.2 g orally every 12 hours) for 10 days + Standard Treatment (ST_s_)^6^ \|   **Standard Treatment for severe patients: (ST_s_)**   1. Strict Isolation 2. Standard Precautions (Hand hygiene, Cough Etiquette, Wear surgical mask) 3. Fluid Therapy 4. Supportive Pharmacotherapy (Antipyretic, Antiallergic, Cough Suppressant) 5. Oxygen supplementation (As required) 6. Invasive ventilation (As required) 7. Antibiotic agents for other associated infections (according to 2019 ATS/IDSA guidelines for non-ICU and ICU patients) 8. Vasopressor support 9. Renal-replacement therapy 10. Treatment of Comorbid Diseases 11. Oseltamivir (75 mg BD) for patient who are tested positive for H1N1   Patients will be assessed for clinical and laboratory improvements in 72 hours of treatment. In case the patient does not respond to the current treatment regimen the patient will be shifted to institute protocol for current practice of treatment.  **Timelines of investigations: Repeated at 72hrs interval**   \| Investigations \| Baseline \| Next 72hrs \| \| --- \| --- \| --- \| \| CBC \| **✔** \|  \| \| LFT \| **✔** \|  \| \| KFT \| **✔** \|  \| \| HBA1C and Blood sugar \| **✔** \|  \| \| RT-PCR for SARS-Cov-2 (until 24hrs apart twice negative) \| **✔** \|  \| \| PT/INR \| **✔** \|  \| \| Serum Electrolytes \| **✔** \|  \| \| ABG \| **✔** \|  \| \| Chest Xray \| **✔** \|  \| \| ECG \| **✔** \|  \| \| Other organ markers as per involvement \| **✔** \|  \|     **Dose Modifications:**  If any serious adverse event is recorded, the participant will be withdrawn from the trial and management will be done accordingly as per institute policy.  **Recording adverse events:**  All adverse events will be recorded in the medical records in the first instance. All adverse events will be recorded with clinical symptoms and accompanied with a simple, brief description of the event, including dates as appropriate. Each adverse event will be assessed for severity, causality, seriousness and expectedness and informed to IEC within 24hours.  **Discontinuation/withdrawal of participants:**  A participant may be withdrawn from trial treatment whenever continued participation is no longer in the participant’s best interests, but the reasons for doing so must be recorded.  Reasons for discontinuing treatment may include:   1. Unacceptable drug toxicity 2. Development of progressive disease 3. Patients withdrawing consent to further trial treatment   **Endpoints:**  **Primary endpoints:**   1. Time to Clinical recovery (TTCR)    - TTCR is defined as the time (in hours) from initiation of study treatment (active or placebo) until normalisation of fever, respiratory rate, and oxygen saturation, and alleviation of cough, sustained for at least 72 hours.    - Normalisation and alleviation criteria: 2. Fever - ≤36.9°C or -axilla, ≤37.2 °C oral 3. Respiratory rate - ≤24/minute on room air 4. Oxygen saturation - >94% on room air 5. Cough- mild or absent on a patient reported scale of severe, moderate, mild, absent 6. Time to SARS-CoV-2 RT-PCR negative in upper respiratory tract specimen 7. Time to laboratory recovery of each organ involvement   **Secondary Endpoints:**   1. All causes mortality 2. Frequency of respiratory progression  - Defined as SPO2≤ 94% on room air or PaO2/FiO2 <300mmHg and requirement for supplemental oxygen or more advanced ventilator support.  1. Time to defervescence (in those with fever at enrolment) 2. Frequency of requirement for supplemental oxygen or non-invasive ventilation 3. Frequency of requirement for mechanical ventilation 4. Frequency of serious adverse events as per AIDS table grade of severity   **Statistical analysis**:  All COVID-19 positive patients will be included in the study after informed consent. Since it is an exploratory trial as COVID-19 being a new disease, all patients who came under the purview of the inclusion criteria within the study period and who have consented for the study will be included. Data will be described as mean+ SD for most of the parameters. Comparisons of the descriptive variables of the two arms will be performed using the Wilcoxon rank sum test for continuous variables and the chi-square or Fisher’s exact test for categorical variables. Primary analysis will include all patients (Intention to treat) and sub-group populations (per-protocol).  **Ethical clearance:**  The present study deals with a new infectious disease which has no definite treatment. Current therapy is based on symptomatic treatment. The present study explores the possibilities of new drugs in SARS-CoV-2 infection. The study will be conducted after IEC approval. Written informed consent will be taken from all participants.  **Safety Outcomes**  Safety outcomes will be determined according to the division of AIDS table for grading severity of adult adverse events (<https://rsc.niaid.nih.gov/clinical-research-sites/daids-adverse-event-grading-tables>), with specific focus on the events of gastrointestinal tract, arrhythmias, myopathies. In case of serious ADRs including death, compensation will be given as per institute protocol. |

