**LABORATORY RESULTS ON FOLLOW UP (*record units if different from those listed)**

| Parameter | Value | Not done | Parameter | Value | Not done |
| --- | --- | --- | --- | --- | --- |
| Haemoglobin (g/L) |  |  | Urine R/M (significant if any) |  |  |
| WBC count (x109/L |  |  | Sodium (mEq/L |  |  |
| Haematocrit (%) |  |  | Potassium (mEq/L) |  |  |
| Platelets (x109/L) |  |  | Calcium(mg/dL) |  |  |
| APTT/PT/INR |  |  | Lactate (mg/dL) |  |  |
| Total bilirubin (mg/dL) |  |  | Procalcitonin (ng/mL) |  |  |
| Direct bilirubin (mg/dL) |  |  | CRP (mg/L) |  |  |
| Albumin (g/dl) |  |  | LDH (U/L) |  |  |
| Globulin (g/dl) |  |  | Creatine kinase (U/L) |  |  |
| SGOT/SGPT (U/L) |  |  | Troponin (ng/mL) |  |  |
| Urea (mg/dL) |  |  | ESR (mm/hr) |  |  |
| Creatinine (mg/dL) |  |  | D-dimer (mg/L) |  |  |
| Others |  |  |  |  |  |

Influenza virus: ☐Positive ☐Negative ☐Not done If positive, type ______________

Coronavirus: ☐ Positive ☐Negative ☐ Not done If positive: ☐ MERS-CoV ☐SARS-CoV-2 ☐Other

Other respiratory pathogen: ☐Positive ☐ Negative ☐Not done If positive, specify:___________

Other pathogen of public health interest detected: If yes, specify: __________________________

Radiological Investigations (if performed):

1. Chest X Ray/CT Performed (report):
2. Ultrasonography:
3. Others

Previous Treatment Regime (If any-to specify group with duaration):

☐Non-Severe Treatment arms (NS-group): Treatment Arm-A: ___________________________

Outcomes:

1. Clinical recovery ☐Yes ☐No
2. Time to 2019-nCoV RT-PCR negative in upper respiratory tract specimen in days (if applicable):
3. Time to defervescence in hours (if applicable)
4. Serious adverse events (specify if any)
5. **Final Clinician’s Impression:**

1. [↑](#footnote-ref-1)
2. **Severe Treatment arms (S-group)**

   **PARTICIPANT ID** I___I I___I I___I I___I I___I -- I___I I___I I___I I___I **Date of enrolment** [__][__]/[__][__]/[__][__][__][__]

   **Day of Hospitalization: _______________ Date of follow-up:** [__][__]/[__][__]/[__][__][__][__]

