   | Urea (mg/dL) |  |  | ESR (mm/hr) |  |  |
   | Creatinine (mg/dL) |  |  | D-dimer (mg/L) |  |  |
   | Others |  |  |  |  |  |

   **Influenza virus**: ☐Positive ☐Negative ☐Not done If positive, type ______________ **Coronavirus:** ☐Positive ☐Negative ☐Not done If positive: ☐MERS-CoV ☐SARS-CoV-2 ☐Other **Other respiratory pathogen**: ☐Positive ☐Negative ☐Not done If positive, specify:____________

   **Other pathogen of public health interest detected**: If yes, specify: __________________________

   **Radiological Investigations** (if performed):

   Chest X Ray/CT Performed (report):

   Ultrasonography:

   Others

   **SUPPORTIVE CARE** Is the patient CURRENTLY receiving any of the following?

   | ICU or High Dependency Unit admission? Yes No Unknown  Date of ICU/HDU admission [__][__]/[__][__]/[__][__][__][__] , ☐Unknown  ICU/HDU discharge date [__][__]/[__][__]/[__][__][__][__],☐Not discharged yet ☐Unknown  Oxygen therapy? ☐Yes ☐No ☐Unknown If yes, complete all below:  O2 flow volume: ☐1-5 L/min ☐6-10 L/min ☐11-15 L/min ☐>15 L/min ☐Unknown  Source of oxygen: ☐Piped ☐Cylinder ☐Concentrator ☐Unknown  Interface: ☐Nasal prongs ☐HF nasal cannula ☐Mask ☐Mask with reservoir ☐CPAP/NIV mask ☐Unknown  Non-invasive ventilation? (e.g. BIPAP, CPAP) ☐Yes ☐No ☐Unknown  Invasive ventilation (Any)? ☐Yes ☐No ☐Unknown  Inotropes/vasopressors? ☐Yes ☐No ☐Unknown  Prone position? ☐Yes ☐No ☐Unknown  Renal replacement therapy (RRT) or dialysis? ☐Yes ☐No ☐Unknown |
   | --- |

   **Previous Treatment Regime** (If any-to specify group with duaration):

   ☐Non-Severe Treatment arms (NS-group): Treatment Arm-A:___________________________

   ☐Non-Severe Treatment arms (NS-group): Treatment Arm-B:___________________________

   ☐Severe Treatment arms (S-group): Treatment Arm-A:___________________________

   ☐Severe Treatment arms (S-group): Treatment Arm-B:___________________________

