   **Outcomes:**

   Clinical recovery ☐Yes ☐No

   Time to 2019-nCoV RT-PCR negative in upper respiratory tract specimen in days (if applicable):

   Time to defervescence in hours(if applicable)

   Serious adverse events (specify if any)

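### All-cause mortality is an endpoint, but deaths are recorded only by exception and neither follow-up form has a dated vital status at day 28

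*Protocol*

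**What the plan says.** Item (e) of the protocol's proposal description puts "All causes mortality" first under Secondary Endpoints, with no time point. The Design paragraph says "Patients will be followed up for a period of 28 days from the day of enrolment", and the total observation period is "28 days from the time of enrolment into the study OR till patient is discharged or death whichever is longer". The Statistical analysis paragraph bases the primary analysis on all patients by intention to treat, with a per-protocol analysis beside it.

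The case report form is part of the same document. The Outcomes blocks of the non-severe and severe follow-up forms hold the same items: clinical recovery (yes or no), time to a negative RT-PCR, time to defervescence, and "Serious adverse events (specify if any", followed by a free-text final impression. The only discharge field on either form is the "ICU/HDU discharge date" on the severe form, which is not hospital discharge. The Adverse Event Log has a fatal outcome code, a grade 5 for death, and start and end dates.

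On leaving, the Dose Modifications paragraph says "If any serious adverse event is recorded, the participant will be withdrawn from the trial". The discontinuation section speaks instead of stopping study treatment. Severe patients who do not respond move to the institute's own protocol, and the flow diagram treats progression there as reaching the end point.

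**The concern.** An intention-to-treat comparison of mortality needs a known status for every randomised patient at a common time. A system that records deaths only when someone reports an event gives a numerator but does not verify the denominator. A patient with no entry may have been alive at day 28 or may simply not have been seen.

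The patients most open to this are those who leave the usual observation path: discharged before day 28, moved to the institute's protocol after non-response, or withdrawn after a serious adverse event. The last two groups are selected for poor prognosis or toxicity, so their missing status is unlikely to be random. The trial is open label, so the decisions behind some exits are made with knowledge of the arm. If status is not collected at the time, it may not be recoverable later, and no analysis plan can supply it.

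**Working it through.** The protocol gives no sample size, mortality rate or event count, so there is no figure to reproduce. The check is a reading of the forms against the endpoint list, followed by an illustration.

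**1. Endpoints against form items.**

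| Secondary endpoint | Item on a follow-up form |
| --- | --- |
| All-cause mortality | None; only the adverse event log, event free text or final impression |
| Respiratory progression | Oxygen saturation with room air or oxygen tick (both forms); oxygen therapy (severe form) |
| Time to defervescence | "Time to defervescence in hours (if applicable" (non-severe form) and the same item on the severe form |
| Oxygen or non-invasive ventilation | Oxygen tick (both); ventilation item (severe form) |
| Mechanical ventilation | Invasive ventilation item (severe form) |
| Serious adverse events | Free text (both) |

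Mortality is the one secondary endpoint with no item of its own on either form. The follow-up forms and the log appear without a removed page between them, so redaction does not explain this.

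**2. What the existing routes can establish.** The log can code a reported death. It cannot confirm that a patient without an entry was alive. Each follow-up form carries a visit date and vital signs, so a last-seen-alive date can be derived while forms are being completed. The forms are indexed by day of hospital stay, and the visible text describes no visit, call or record check after discharge.

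**3. The exits.**
- Discharge before day 28: observation should continue under the whichever-is-longer rule, but no means is given.
- Shift to the institute's protocol: follow-up is not said to stop, but nothing says how later status is recorded.
- Serious adverse event: one wording takes the patient out of the trial, the other ends study treatment only. The two lead to different data on the same patient.

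**4. Illustration. Every rate here is assumed; none comes from the protocol.** Let p be true 28-day mortality, e the share of an arm that exits, r the risk of death after exit, and m the share of those deaths that go unrecorded. If patients without an entry are counted as alive:

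observed mortality = p − e × r × m

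Take p = 20% in both arms and r = 30%.

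| Exits, control / active | m | Control | Active | False difference |
| --- | --- | --- | --- | --- |
| 10% / 30% | 1 | 20 − 3 = 17% | 20 − 9 = 11% | 6 points, favours active |
| 10% / 30% | 0.5 | 20 − 1.5 = 18.5% | 20 − 4.5 = 15.5% | 3 points, favours active |
| 20% / 20% | 1 | 20 − 6 = 14% | 14% | none, but both understated |
| 30% / 10% | 1 | 11% | 17% | 6 points, favours control |

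Dropping the unknowns does not repair the first row: 17/90 = 18.9% against 11/70 = 15.7%, still about 3 points apart.

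If those who exit share the arm's overall risk (r = 20%) and all their deaths are missed, observed mortality is 20% × (1 − e). With e from 10% to 40% that is 18% down to 12%. With capture of 90% in one arm and 70% in the other it is 18% against 14%, a false 4 points. In this case dropping the unknowns does restore 20% in both arms (18/90 and 14/70). The bias therefore depends on how missing status is handled and on whether exits are sicker than the rest.

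**5. Time origin.** Non-severe patients who worsen are randomised again into the severe group with new consent. A patient who moves on day 5 and is followed to day 28 from the first randomisation has 28 − 5 = 23 days in the severe comparison, against 28 for a direct entrant.

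**The case against.** The strongest reply is that the protocol does not abandon these patients. It plans 28 days for everyone, and an early discharge does not end observation. A shift is a change of treatment, and no text says the patient leaves the trial. Deaths have several routes into the record: log codes with dates, free text on both forms, the final impression, and the requirement that all adverse events go into the medical record and be reported to the ethics committee within 24 hours. No text exempts deaths from COVID-19 itself. The participant information sheet and consent form, which might describe contact after discharge, are not in the reviewed text. Mortality is also a secondary endpoint in a trial that calls itself exploratory.

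Most of this stands, and it limits the point. A reader might infer that missing status is scored as survival and that this favours the more toxic arm. The documents support neither inference. No rule scores missing status as alive, and such a rule would commonly sit in a statistical analysis plan, which is not shown. Shift for non-response applies in every severe arm, so controls could exit as often or more often. Nor can it be said that contact after discharge is absent from the whole plan, only from the visible text.

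The reply does not supply the missing field. A stated intention to follow for 28 days, without a place to record the result, does not separate a confirmed survivor from a patient not seen again. An analysis plan can choose a rule for unknown status but cannot create the status.

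**Conclusion.** The point holds in this form: mortality is captured by exception, no form has a dated vital status, and the two withdrawal wordings conflict on whether a patient with a serious adverse event remains under observation. Mortality may be understated, and the comparison may be biased if exits differ by arm. The size cannot be derived from the protocol. The illustrated range, from no false difference to 6 points in either direction, rests wholly on assumed exit shares, post-exit risks and capture. It shows that the effect could matter, not that it will occur. In-hospital deaths after a shift are the likeliest to be recovered from hospital records; deaths after discharge, or after removal from the trial, are the most exposed.

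**What to change.** - Add to the Outcomes block of both follow-up forms: vital status at day 28 (alive, dead, unknown), date of death or date last known alive, and dates of hospital discharge, shift and withdrawal.
- Reconcile the withdrawal wordings in the Dose Modifications paragraph and the discontinuation section. Whatever the clinical rule on treatment, state that vital status is still collected after treatment is stopped or shifted, unless the patient withdraws consent to follow-up.
- Obtain day-28 status for every randomised patient by one telephone or record check. Count the 28 days from the randomisation that defines each comparison; for patients randomised again into the severe group, also record status 28 days after the second randomisation.
- Analyse mortality from this field, with the adverse event log as a cross-check.

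The cost is a form revision and one short check per patient who has left hospital. No treatment changes.

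### The mechanical-ventilation endpoint does not count death, and the oxygen/NIV endpoint omits invasive ventilation, so a worse outcome can be scored as a non-event

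*Protocol*

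**What the plan says.** All of this is in item (e) of the protocol's brief description of the proposal, under Secondary Endpoints, Statistical analysis and Total duration of observation.

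- Three respiratory endpoints are simple frequencies. Respiratory progression is "Defined as SPO2≤ 94% on room air or PaO2/FiO2 <300mmHg and requirement for supplemental oxygen or more advanced ventilator support". The other two are "Frequency of requirement for supplemental oxygen or non-invasive ventilation" and "Frequency of requirement for mechanical ventilation".
- Mortality is a separate entry in the same list: "All causes mortality". It is not combined with any respiratory endpoint.
- The only test named for binary data is "the chi-square or Fisher’s exact test for categorical variables". The primary analysis is said to include all patients by intention to treat, with a per-protocol analysis besides.
- Observation lasts "28 days from the time of enrolment into the study OR till patient is discharged or death whichever is longer".

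The protocol gives no rule for a patient who dies before the respiratory event could occur. It also states no sample size, event rate, significance level or target difference for these endpoints.

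**The concern.** There are two separate gaps.

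The first is death. With everyone in the denominator and no death component, a patient who dies without being ventilated falls in the same cell as one who recovered without needing it. If such deaths are unequal between arms, the arm with more of them gains on the ventilation endpoint. The severe group admits septic shock and multiple organ dysfunction, so death without ventilation is plausible there. The trial is open label and ventilation is given as required, so a count of ventilated patients also depends on care decisions.

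The second is the level of support. The progression definition closes with "and requirement for supplemental oxygen or more advanced ventilator support", so higher support counts. The oxygen/NIV endpoint in the same list has no such clause. Read literally, a patient intubated without prior oxygen or NIV is a non-event on it.

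What is at stake is the direction of a reported comparison: fewer patients ventilated could be presented as benefit when part of the difference is that more died first.

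**Working it through.** **Which patient counts where, on the literal wording**

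| Patient | Mechanical ventilation | Oxygen/NIV | Respiratory progression |
| --- | --- | --- | --- |
| Dies with no respiratory support | non-event | non-event | non-event |
| Given oxygen, then dies unventilated | non-event | event | event if hypoxaemia criterion met |
| Goes straight to invasive ventilation | event | non-event | event if hypoxaemia criterion met |

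The death problem therefore lies mainly in the ventilation endpoint. The direct-intubation problem lies only in the oxygen/NIV endpoint.

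**Inputs.** The protocol has no figure to reproduce. All rates and arm sizes below are assumptions. Let d be the probability of dying unventilated, with arm B having more such deaths than arm A.

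**Model 1: ventilation-or-death fixed at 30% in both arms.** Ventilation frequency = 0.30 − d.

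- d = 5% v 10%: 25% v 20%, ratio 0.80
- d = 5% v 15%: 25% v 15%, ratio 0.60
- d = 10% v 20%: 20% v 10%, ratio 0.50

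**Model 2: ventilation risk v is the same in both arms among patients who do not die unventilated.** Ventilation = (1 − d)·v. Ventilation or death = d + (1 − d)·v.

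- With v = 20% and d = 5% v 15%, ventilation is 0.95 × 0.20 = 19% v 0.85 × 0.20 = 17%, ratio 0.89. Arm B looks 2 points better.
- Counting death gives 5% + 19% = 24% v 15% + 17% = 32%. Arm B is 8 points worse.
- With v at 20% and 40%, arm A deaths 5% and arm B deaths 10%, 15% or 25%, arm B looks 1 to 8 points better as written, and is 3 to 16 points worse with death counted.

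**Chance of a nominally significant result favouring arm B** (two-sided 5%, exact enumeration of two binomials; the z-test is the uncorrected chi-square)

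| Ventilation, A v B | z-test, 50 per arm | Fisher, 50 | z-test, 100 | Fisher, 100 |
| --- | --- | --- | --- | --- |
| 25% v 20% (model 1) | 9% | 6% | 13% | 10% |
| 25% v 15% (model 1) | 24% | 17% | 43% | 36% |
| 20% v 10% (model 1) | 30% | 19% | 52% | 44% |
| 19% v 17% (model 2) | 4.7% | 2.5% | 5.7% | 3.9% |

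For reference, with 19% in both arms the same calculation at 50 per arm gives 2.6% (z-test) and 1.4% (Fisher).

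**Oxygen/NIV.** If 50% of patients need support and 10% to 30% of those go straight to invasive ventilation, the endpoint reads 0.50 × 0.90 = 45% down to 0.50 × 0.70 = 35%. Progression stays at 50% if all of them meet the hypoxaemia criterion.

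**The case against.** A reader might infer that all three respiratory endpoints score both unventilated deaths and direct intubations as event-free. The table above shows otherwise. A directly intubated patient is an event under mechanical ventilation and can be one under progression, and oxygen given before death already counts under oxygen/NIV.

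Other objections, and what stands of each:

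- *Separate endpoints for lower and higher support are a deliberate tiering.* Possible, but the text does not say so, and the progression definition takes the opposite course. The inconsistency needs one clarifying phrase.
- *The wording speaks of requirement, not receipt, so a patient who needed ventilation and died first is not excluded.* This stands as an ambiguity. The case report form records what the patient is receiving, which points towards receipt. The non-event status is a consequence of the literal wording, not a stated rule.
- *Handling of death belongs in a statistical analysis plan, which is not at hand.* Partly. An analysis plan could set a rule, but what counts as an event is already written here as an endpoint definition.
- *Mortality is reported separately, and nothing decisive rests on these endpoints.* Correct, and it lowers the priority. It shows the deaths but leaves the ventilation comparison distorted.
- *The larger percentages are near a worst case.* This stands. Fixing the composite at 30% makes each extra unventilated death remove exactly one ventilation, and nothing in the protocol supports that. Nor are these figures type I error rates for the endpoint as written, because the true ventilation frequencies differ in those scenarios.
- *Patients already ventilated at entry cannot die unventilated.* True. Need of mechanical ventilation is itself a severity criterion, so the share of the severe group exposed to the problem is unknown.

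**Conclusion.** The concern holds in a limited form. The ventilation endpoint omits death, so on its literal reading it favours an arm with more unventilated deaths. The oxygen/NIV endpoint omits invasive ventilation, at odds with the progression definition beside it.

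The direction is clear whenever unventilated deaths differ between arms and reduce the number at risk of ventilation. The size is not known. For 5% versus 15% unventilated deaths it runs from 2 points (19% v 17%) to 10 points (25% v 15%), depending on which of two assumed models applies. With 50 per arm, the chance of a misleading significant result runs from 4.7% to 24% by z-test and from 2.5% to 17% by Fisher. The upper figures should not be quoted without the assumption behind them.

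The documents do not support saying that the protocol instructs that deaths be counted as successes, or that every respiratory endpoint is equally affected. As these are secondary endpoints in a trial described as exploratory, with mortality reported separately, this is a worthwhile correction of modest priority.

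**What to change.** Reword two endpoints:

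1. Mechanical ventilation or death.
2. Supplemental oxygen, NIV or higher support, or death.

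Compare them with the chi-square or Fisher test already named, and list each component by arm beside all-cause mortality. The progression endpoint can stay as it is. Adding death to it is debatable, because deaths from septic shock or from liver or renal failure would then be scored as respiratory progression.

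The cost is a line of wording per endpoint. The severe-group follow-up form already records oxygen, NIV and invasive ventilation, and the adverse event log has a fatal outcome code. The non-severe follow-up form has only a room-air or oxygen tick box beside saturation, so it should be confirmed that higher support is captured for those patients. The endpoints as now written need that too.

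The downside is that a composite mixes support with death and can hide a shift between them. In model 1 it reads 30% v 30% even when unventilated deaths are 5% v 15%. The component listing is therefore a necessary part of the change.
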